## Abstract

**Introduction:**

The newer glucose-lowering therapies for type 2 diabetes (T2D), the glucagon-like peptide-1 receptor agonists (GLP1-RAs) and the sodium-glucose co-transporter 2 inhibitors (SGLT2i), have additional clinical benefits beyond improving glycaemic control; promoting weight loss, addressing associated cardiovascular risk factors and reducing macrovascular and microvascular complications. Considering their independent mechanisms of actions, there is a potential for significant synergy with combination therapy, yet limited data exist. This 32-week randomised, double-blind, placebo-controlled trial will gain mechanistic insight into the effects of coadministration of exenatide QW, a weekly subcutaneous GLP1-RA, with dapagliflozin, a once daily oral SGLT2i, on the dynamic, adaptive changes in energy balance, total, regional and organ-specific fat mass and multiorgan insulin sensitivity.

**Methods and analysis:**

110 obese patients with diagnosed T2D (glycated haemoglobin, HbA_1c_ ≥48 mmol/mol) will be treated for 32 weeks with dapagliflozin (10 mg once daily either alone or in combination with exenatide QW (2 mg once weekly); active treatments will be compared with a control group (placebo tablet and sham injection). The primary objective of the study is to compare the adjusted mean reduction in total body fat mass (determined by dual-energy X-ray absorptiometry, DEXA) from baseline following 32 weeks of treatment with exenatide QW and dapagliflozin versus dapagliflozin alone compared with control (placebo). Secondary outcome measures include changes in (1) *energy balance* (energy intake and energy expenditure measured by indirect calorimetry); (2) *appetite* (between and within meals) and satiety quotient; (3) *body composition* including visceral adipose tissue, subcutaneous adipose tissue, liver and pancreatic fat. Exploratory outcome measures include *metabolic changes* in hepatic and peripheral insulin sensitivity (using a two-stage hyperinsulinaemic, euglycaemic clamp), *central nervous system responses* to food images using blood oxygen level-dependent (BOLD) functional MRI (fMRI) and *changes in cardiovascular function* (using transthoracic echocardiography, cardiac MR and duplex ultrasonography).

**Ethics and dissemination:**

This study has been approved by the North West Liverpool Central Research Ethics Committee (14/NW/1147) and is conducted in accordance with the Declaration of Helsinki and the Good Clinical Practice. Results from the study will be published in peer-reviewed scientific and open access journals and/or presented at scientific conferences and summarised for distribution to the participants.

**Trial sponsor:**

University of Liverpool.

**Trial registration number:**

ISRCTN 52028580; EUDRACT number 2015-005242-60.

Strengths and limitations of this studyThis is the first study to assess the effects of sodium-glucose co-transporter 2 inhibitor (SGLT2i) and glucagon-like peptide-1 receptor agonist (GLP1-RA) combination therapy on changes in body composition and appetite in a randomised controlled trial design incorporating short-term and long-term effects.We employ an array of experimental techniques to identify the underlying biological basis of these changes and to yield some mechanistic insight into the metabolic, cardiac and vascular effects of combination therapy.The study is not designed to examine the individual effects of each agent but rather to investigate the compensatory mechanisms that additional GLP-1 RA therapy to SGLT2i therapy may induce.The relatively small sample size provides sufficient power to answer the primary research question.The relatively low sensitivity of even ‘*state-of-the-art*’ research methods for detecting changes in energy intake, expenditure and energy balance mean that subtle changes may be missed.

## Background and rationale

Type 2 diabetes (T2D) is closely related to obesity: their prevalence is rising in parallel, synergistically accelerating and increasing the severity of diabetes-related complications.^1^ Weight loss is therefore a primary therapeutic target in the management of patients with T2D. While some glucose-lowering treatments are associated with weight gain (eg, sulfonylureas, thiazolidinediones and insulin), two recent classes of therapeutic agents for T2D, namely, the glucagon-like peptide-1 receptor agonists (GLP1-RAs) and the sodium-glucose co-transporter 2 inhibitors (SGLT2i), are associated with weight loss, achieved via different mechanisms: increased urinary glucose loss for SGLT2i, and promotion of satiety for GLP-1 RAs.

Pharmacological inhibition of SGLT2 *reduces renal glucose reabsorption* in an insulin-independent mechanism promoting a daily urinary glucose excretion (UGE) of ~75 g, an energy deficit of ~300 kcal and a diuresis of ~400 mL.^2 3^ GLP1-RAs confer similar therapeutic benefits operating via distinct mechanisms: *improving glycaemic control* (by enhancing glucose-dependent insulin secretion and inhibiting hepatic glucose production)^4^ and *reducing body weight* via a central effect (promoting satiety via the hypothalamus).^5 6^ The glucose-lowering effects of SGLTi maybe attenuated by increased endogenous (hepatic) glucose production,^7 8^ partially explained by a compensatory hyperglucagonaemia.^9^ It is also unclear why the magnitude of weight loss with SGLT2i therapy is not commensurate with the expected weight loss based on the determined caloric loss, suggesting compensatory or adaptative changes in energy intake and energy expenditure that attenuate the energy imbalance.^10 11^

Overall, the limited available evidence demonstrates the additive benefits of combination therapy with a GLP-1 RA and SGLT2 inhibitor on glycaemic improvement and weight.^12–14^ Further studies are needed to elucidate their combined effects on metabolic and cardiovascular disease. The central hypothesis of this mechanistic study is that coadministration of exenatide once weekly (QW; a GLP-1 RA) with dapagliflozin (an SGLT2i) treatment will offset the potentially (mal)adaptive compensatory metabolic and appetitive responses occurring with dapagliflozin alone. Specifically, we anticipate that GLP-1 RAs can attenuate the increased hepatic glucose production due to hyperglucagonaemia and possible compensatory increases in appetite that arise with SGLT2i therapy (figure 1).

**Figure 1 F1:**
[figure not shown]
Potential synergy with sodium-glucose co-transporter 2 (SGLT2) inhibitors and glucagon-like peptide-1 (GLP-1) receptor agonists.

## Primary objective

The primary objective of the study is to compare the adjusted mean reduction in total body fat mass (determined by dual-energy X-ray absorptiometry, DEXA) from baseline following 32 weeks of treatment with exenatide QW and dapagliflozin versus dapagliflozin alone compared with control (placebo).

## Secondary objectives

The key secondary objectives are to assess the adjusted mean change from baseline of:

Metabolic measuresHbA_1c_ (mmol/mol).Fasting glucose (mmol/L).Total Low-density lipoproteins (LDL) and High-density lipoproteins (HDL) cholesterol and triglycerides (mmol/L).Twenty-four hour urinary glucose excretion(UGE) (g/dL).Changes in energy balanceFood intake (g and kcal) at *ad libitum* meals.Total energy expenditure: Measured by indirect calorimetry using a ventilated hood system and derived using the Weir equation.^15 16^Physical activity: Measured by a multisensor array (daily average step count, and time spent in domains of physical activity (METS)).Eating behaviourVisual Analogue Scale (VAS): A seven-component VAS questionnaire used to assess hunger, fullness, prospective food consumption and desire to eat.Satiety quotient: Measured using VAS ratings and calculated as the difference in hunger pre-meal and post-meal divided by the within meal caloric intake.Psychology of appetite questionnaire scores.Changes in body compositionReduction in total body weight (kg).Total fat volume (L), regional fat volumes (visceral fat and subcutaneous fat volume) and tissue-specific fat content (liver and pancreatic fat) measured by MRI scanning.Changes in lean body mass measured by DEXA and MRI.Changes in cardiovascular variablesBlood pressure (mm Hg).

In addition, this study will assess treatment compliance at 28-day intervals, based on the number of injections administered and returned tablet counts.

## Exploratory endpoints

These are to be analysed and presented separately to primary and secondary outcome measures.

Metabolic measuresEndogenous (hepatic) glucose production, during a euglycaemic low-dose insulin clamp combined with a constant infusion of [6,6 ^2^H_2_] glucose.Peripheral insulin sensitivity, measured by glucose uptake (Rd) and glucose metabolic clearance rate (MCR), during a euglycaemic high-dose insulin clamp combined with a constant infusion of [6,6 ^2^H_2_] glucose.Changes in energy balanceTotal energy expenditure: Measured by doubly labelled water.Changes in cardiovascular variables:Echocardiographic derived measures of left and right ventricular structure and function, including systolic and diastolic strain (rate) and twist mechanics.Carotid artery intima media thickness (cIMT; mm) and brachial artery flow-mediated dilatation (FMD) using duplex ultrasonography.MRI derived measures of cardiac structure and function.Changes in body compositionLiver fibrosis measured by multiparametric MRI scanning.Changes in Central nervous system (CNS) responseDifferences in neuronal activity in CNS reward and satiety circuits (including striatum, amygdala, orbitofrontal cortex, insula, hypothalamus) as represented by BOLD (blood oxygen level-dependent) functional MRI (fMRI) signal change.

## Safety objective

The type and frequency of adverse events will be reported for all treatment groups.

## Methods and analysis

### Overall design, investigational plan and study population

This is a 32-week outpatient, double-blind, parallel group, randomised placebo-controlled mechanistic study of exenatide QW (GLP1-RA) and dapagliflozin (SGLT2i) treatment. One hundred and ten participants with obesity and T2D will be recruited: male and female, aged 18–65 years, Body mass index (BMI) 30–50 kg/m^2^, with glycated haemoglobin (HbA_1c_) ≥6.5% but ≤11% (48–97 mmol/mol; see table 1 for complete criteria). Each participant will have 13 study visits. Participants will be randomised equally to each of the three treatment arms (figure 2).

**Table 1 T1:** Study inclusion and exclusion criteria

**INCLUSION CRITERIA** Males or females, age 18–65 years. A clinical diagnosis of type 2 diabetes. Glycosylated haemoglobin (HbA1c) ≥6.5% but ≤11% (48–97 mmol/mol). Currently treated with either diet or any combination of metformin, DPP-IV inhibitors* and sulfonylureas (excluding patients treated with pioglitazone or insulin). *DPP-IV inhibitors will require wash out period of 4 weeks. BMI 30–50 kg/m^2^. Patients who are receiving the following medications must be on stable treatment regimen for a minimum of 2 months prior to screening: Thyroid hormone replacement Antidepressants **EXCLUSION CRITERIA** **Medical History and Concurrent Diseases** Type 1 diabetes mellitus. History of diabetic ketoacidosis or hyperosmolar non-ketotic coma. Renal impairment: eGFR less than 60 mL/min/1.73 m^2^. Familial renal glucosuria. Clinically significant abnormal free T4 or patients needing initiation or adjustment of thyroid treatment according to the investigator. Severe uncontrolled hypertension ≥180 mm Hg and/or diastolic ≥110 mm Hg. Congestive heart failure class III-IV. Recent (<6 months) myocardial infarction. Known chronic liver disease (other than hepatic steatosis). Significant cardiac dysrhythmias (including pacemaker or ICD). Previous stroke. History of seizures or unexplained syncope. History of, or currently have, acute or chronic pancreatitis. History of malignancy (with the exception of basal and squamous cell carcinoma of the skin) within the last 5 years. History of medullary thyroid carcinoma or MEN2 (Multiple endocrine neoplasia type 2) or family history of medullary thyroid carcinoma or MEN2. History of gastric bypass surgery or gastric banding surgery, or either procedure is planned during the time period of the study. Patient, who in the judgement of the investigator, may be at risk of dehydration or volume depletion (hypovolaemia) that may affect the patient’s safety and/or the interpretation of efficacy or safety data. Presence of any other medical condition that would, in the opinion of the investigator or their clinician, preclude safe participation in the study. This decision should be informed by dapagliflozin and exenatide precautions for use statements which will be provided to all clinicians and the research team. Alcohol consumption in excess of 21 units/week females, 28 units/week males. Current smoker (including electronic cigarettes) or having ceased smoking in the last 6 months. Any history of a pacemaker or implantable cardioverter defibrillator (ICD). Patients with a history of diabetic foot ulcers or previous (lower limb) digital amputations.	Patients currently taking part in a structured weight loss programme such as weight watchers or slimming world (excluding those on weight management programmes as part of their diabetes care). Patients who score over 4 restraint subscale of the Dutch Eating Behaviour Questionnaire. Patients who score over 27 on the Binge Eating Scale. **Physical and Laboratory Test Findings** ALT>3×upper limit of normal (ULN). AST>3×ULN. Bilirubin>2×ULN. Haemoglobin ≤10.5 g/dL (≤105 g/L) for men; haemoglobin ≤9.5 g/dL (≤95 g/L) for women. History of unexplained microscopic or macroscopic haematuria at screening, confirmed by follow-up sample a next scheduled visit, where according to the investigator a satisfactory evaluation of haematuria has not been conducted. Weight <60 kg and >200 kg (due to DEXA limitations). BMI <30 kg/m^2^ and >50 kg/m^2^. Recent major change in body weight (>3 kg loss or gain in preceding month). **Allergies and Adverse Drug Reactions** Subjects with a history of any serious hypersensitivity reaction to GLP1-RA or SGLT2 inhibitor. Participant should have no allergies against metacresol (the preservative in insulin vial). History of anaphylaxis to food. Known food allergies or food intolerance. Known hypersensitivity to heparin. Known hypersensitivity to intravenous catheter equipment. **Sex and Reproductive Status** Females of childbearing age who are not using adequate contraceptive methods or who are planning a pregnancy in the next 44 weeks (study duration plus 12 weeks). Women who are pregnant or breast feeding. Sexually active fertile men not using effective birth control if their partners are WOCBP. **Prohibited Treatments and/or Therapies** Diabetes treated with pioglitazone, SGLT2 inhibitors, GLP-1 analogues or insulin. Treatment with SGLT2 inhibitor, GLP1 RA or subcutaneous insulin injections 3 months before screening. Any weight loss medication (eg, orlistat) within 3 months prior to screening. Use of any drug that might affect body weight or appetite (including antipsychotics or corticosteroids) within 3 months prior to screening. Patients who are currently receiving a loop diuretic that cannot be discontinued. **Other Exclusion Criteria** Active or previous substance abuse or dependence. Prisoners or subjects who are involuntarily incarcerated. Subjects who are compulsorily detained for treatment of either a psychiatric or physical (eg, infectious disease) illness. Dislike >25% of the study foods. Participation in other studies (within the past 30 days). *In situations where the patient has a contraindication to MR scanning, they will be randomised to the study but excluded from MR scanning only. The primary outcome measurement of fat mass can be derived from DEXA*.

ALT, Alanine transaminase; AST, Aspartate transaminase; BMI, Body mass index; DEXA, dual-energy X-ray absorptiometry; eGFR, estimated glomerular filtration rate; GLP1-RA, glucagon-like peptide-1 receptor agonist; SGLT2i, sodium-glucose co-transporter 2 inhibitors; WOCBP, Women of childbearing potential.

**Figure 2 F2:**
[figure not shown]
Study schematic.

### Patient and public involvement

Patients were involved in the design and conduct of the trial. During the feasibility stage, choice of outcome measures, the number of study visits and methods of recruitment were informed through discussions with patients in the clinical setting and attendance at local diabetes education sessions. During the trial, a patient joined the independent trial steering committee (TSC). Once the trial has been published, a clear ‘plain English’ summary of the findings will be created so that they are widely available to participants and the wider patient groups. These will be presented to attendees at diabetes awareness days at the hospital and within the community.

### Sample size

This trial will examine exenatide QW, a weekly GLP1-RA, added to dapagliflozin versus sham saline injection added to dapagliflozin for an intervention period, of 32 weeks compared with a control group (placebo tablet and sham injection).

**Arm A:** Placebo tablet once daily and sham injection once weekly.**Arm B:** SGLT2 (dapagliflozin 10 mg once daily plus sham injection once weekly).**Arm C:** SGLT2+GLP1 RA (dapagliflozin 10 mg plus exenatide 2 mg once weekly injection).

The sample sizes have been calculated in order to conduct the following two comparisons:

Arm B (dapagliflozin) vs A (placebo).Arm B (dapagliflozin) vs C (dapagliflozin and exenatide).

These comparisons are selected to answer the key question of interest; although the study will not provide comparisons between arms C and A, nor will they be reported.

The original sample size calculation was carried out using Stata V.14 software (Stata Statistical Software: Release 14. College Station, Texas, USA: StataCorp LP). For both comparisons, a 1.5 kg in the change in body fat mass is considered a clinically relevant difference. From previous data, the within patient SD for the change in total body fat between baseline and 32 weeks is estimated as 1.8 kg.^17^ From this, a between-patient SD of 2.55 kg was computed. Using a two-group test with equal means (assuming 80% power and one-sided 5% significance level), 36 patients per treatment arm were estimated to be required in order to adequately power the planned analysis (assuming effect size of 0.59). Using these calculations and an anticipated 10% attrition and patient dropout rate, the original sample size was set at 120 participants.

As a result of the COVID-19 pandemic, however, 15 active patients were lost to follow-up and a revised sample size calculation was implemented, reducing the original sample size from 120 patients to 110 randomised patients in order to maintain meaningful results within the remaining timeframe of the study. Using the same clinically relevant difference of 1.5 kg, significance level and power, the between-patient SD would be 2.42 kg, giving an effect size of 0.62. Assuming 80% power, a minimum of 33 patients per treatment arm are required. Allowing for an anticipated 11% attrition rate/dropout rate, a total of 110 patients are required (calculated using NQuery V.8.1.2.0).

Recruitment will take place over 44 months in Liverpool University Hospital NHS Foundation Trust (Aintree site), Liverpool, UK. Participants will be recruited either from existing databases of volunteer patients, diabetes clinics in the hospital and community and by advertisement in the local press and social media.

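### The 80% power at 33 per arm rests on an unsourced SD of 2.42 kg; the only sourced input, 1.8 kg, is labelled ambiguously and gives about 96% or about 76%, depending on what it measures.

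*Protocol article*

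**What the plan says.** All of this is in the Protocol article, Sample size. For both planned comparisons (B versus A, and B versus C), "a 1.5 kg in the change in body fat mass is considered a clinically relevant difference". The variability input comes with a literature citation: "the within patient SD for the change in total body fat between baseline and 32 weeks is estimated as 1.8 kg". The next sentence reads "From this, a between-patient SD of 2.55 kg was computed", with no formula shown. The calculation is made "assuming 80% power and one-sided 5% significance level", and "36 patients per treatment arm were estimated to be required", "assuming effect size of 0.59". With "an anticipated 10% attrition and patient dropout rate, the original sample size was set at 120 participants".

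After 15 active patients were lost to follow-up in the pandemic, the calculation was redone to fit the remaining time. Difference, significance level and power are said to be unchanged, but now "the between-patient SD would be 2.42 kg, giving an effect size of 0.62". This leads to 33 per arm and, with 11% attrition, 110 randomised.

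The Analysis section plans a regression of the week 32 value on treatment with baseline as covariate. The strengths and limitations box says that the small sample gives enough power for the primary question.

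**The concern.** A two-group comparison of change needs one SD: that of individual 32-week changes across patients within an arm, or the smaller residual SD if baseline is adjusted for. The section gives three values that could be read as this SD (1.8, 2.55 and 2.42 kg), and its labels do not fit together. The source figure is called within-patient and also an SD of the change, and the figure computed from it is called between-patient. If the 1.8 kg is already the SD of change, multiplying by √2 counts the difference of two measurements twice.

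The later move to 2.42 kg matters more for the current design. It is the only input said to have changed, and it alone takes the requirement from 36 to 33 per arm. No data or derivation is given for it. At stake is whether the power claimed for the primary comparison has any support in the document.

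**Working it through.** **Inputs (Protocol article, Sample size):** difference 1.5 kg; one-sided α 5%; power 80%; SDs 1.8, 2.55 and 2.42 kg; 36, then 33 per arm; attrition 10%, then 11%.

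**Formulas.** Normal approximation: n per arm = 2(1.645 + 0.842)²/d² = 12.37/d², with d = 1.5/SD. Power at n per arm is Φ(d√(n/2) − 1.645). The t figures below come from the noncentral-t two-sample test.

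**1. The plan's figures reproduce from its stated SDs.**
- 1.8 × √2 = 2.546, rounded to 2.55; d = 1.5/2.55 = 0.588; n = 12.37/0.346 = 35.7, so 36 (t: 36.4). 3 × 36 = 108, and 108/0.9 = 120.
- d = 1.5/2.42 = 0.620; n = 12.37/0.384 = 32.2, so 33 (t: 32.9). 3 × 33 = 99, and 99 × 1.11 = 109.9, so 110. Dividing instead, 99/0.89 = 111.2, so 112; the gap is trivial, since 110 × 0.89/3 = 32.6 completers per arm.

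The arithmetic from SD to sample size is sound. The question is which SD goes in.

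**2. Reading A: 1.8 kg is the SD of individual changes.** It goes in directly: d = 1.5/1.8 = 0.833; n = 12.37/0.694 = 17.8, so 18 (t: 19). The √2 step is then wrong.

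**3. Reading B: 1.8 kg is the within-patient residual SD from the baseline and week 32 measurements.** Let dᵢ be patient i's change. With patient and time effects removed, each patient leaves two residuals of ±(dᵢ − d̄)/2. The residual sum of squares is Σ(dᵢ − d̄)²/2 on n − 1 degrees of freedom, so the residual variance is exactly half the variance of the changes. Hence SD of change = √2 × 1.8 = 2.55 kg. This already includes variation between patients in true fat loss, because that variation sits in the same residual. The step is then right, and the result is the spread of changes across patients.

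**4. Power for 1.5 kg, one-sided 5%, 33 per arm.**

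| SD of change | Basis | Normal | t |
|---|---|---|---|
| 1.8 kg | Reading A | 95.9% | 95.6% |
| 2.55 kg | Reading B | 77.2% | 76.4% |
| 2.42 kg | Current calculation, no source | 80.9% | 80.1% |

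**5. Where 2.42 kg could come from.** It is not 1.8 × √2; reversing that step gives 2.42/√2 = 1.71 kg, which appears nowhere. Solving the t-test for the SD that gives 80% power at 33 per arm yields 2.424 kg (d = 0.619). The stated 2.42 kg and 0.62 agree with that solution.

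**The case against.** **The derivation may be correct.** Mis-derivation is not established. Reading B fits the within-patient label and the baseline-to-week-32 interval, and under it 2.55 kg is the right SD. The cited study, which would decide the matter, is not at hand. This stands. A reader might infer that the √2 step is wrong however 1.8 kg is understood, because it would leave out variation in true fat loss. That would hold only if 1.8 kg were pure short-term measurement error. The document does not say so, and step 3 shows that a residual SD from two time points already contains that variation. Power figures well below 76%, obtained by adding a further true-response SD, therefore have no support here.

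**An error in the √2 step would be conservative.** This is true under Reading A, where power is about 96%. It does not rescue the stated 80%, which comes from 2.42 kg.

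**The 2.55 kg calculation has been superseded, and an article may leave the source of 2.42 kg to the full protocol.** The first half is right: 110 rests on 2.42 kg. The second half carries less weight. The article cites a source for the first SD, says that difference, level and power are unchanged, and then prints a different SD for the same quantity without a reason.

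**No estimate or test changes.** This is correct: the baseline-adjusted analysis does not use the planning SD. Only the power claim is affected.

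**Conclusion.** The point holds in a limited form. The labels on 1.8 kg and 2.55 kg cannot be reconciled as written, and the document does not show which reading is meant. On either of the two readings, 33 per arm does not have the stated 80% power: it has about 96% (SD 1.8 kg) or about 76% (SD 2.55 kg). The 80% appears only with 2.42 kg, which has no stated source and does not follow from 1.8 kg.

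A reader might go on to conclude that 2.42 kg was solved back from the number of patients still attainable. The match with 2.424 kg and the setting of the revision are consistent with that, but the document does not prove it. Nor does it show that the trial is underpowered; that depends on what 1.8 kg measures.

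The figures assume a two-sample t-test on change at the plan's own one-sided 5% level with 33 completers per arm. Adjustment for baseline cannot raise the residual SD above the SD of change (apart from one lost degree of freedom), so the planned analysis may do somewhat better than the table shows.

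**What to change.** In Sample size:

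- State what the 1.8 kg measures in the cited study: the SD of individual changes, or a within-patient residual SD.
- Put the resulting SD of 32-week change, or the residual SD after baseline adjustment, directly into the two-group calculation. Show the √2 step only if 1.8 kg is a within-patient residual SD, and name the result the SD of change.
- Give the data behind 2.42 kg, or withdraw it.
- Restate effect size and power at the planned completers (33 per arm, or 32.6 if 11% of 110 drop out). If 2.55 kg stands, that is an effect size of 0.59 and about 76% power. Bring the sufficiency claim in the strengths and limitations box into line.

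A blinded SD of change from patients who already have both DEXA scans could inform the value, but pooling the arms adds the spread between arm means. If the three means are 1.5 kg apart, as planned for both comparisons, that spread has variance (1.5² + 0 + 1.5²)/3 = 1.5. A true 2.55 kg would then appear as √(2.55² + 1.5) = 2.83 kg, and 1.8 kg as √(1.8² + 1.5) = 2.18 kg. The pooled value must be corrected for this.

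The cost is some rewording and one recalculation, and the stated power may fall by about four points. The 110 randomised stay, no patients are added, and a blinded look at the SD spends no alpha.

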##### Significance levels

For the analysis of the primary outcome, statistical significance will be tested using Hochberg’s procedure, a hierarchical analysis approach for the primary outcomes of (1) exenatide QW and dapagliflozin compared with placebo control, (2) dapagliflozin alone compared with placebo control. Here comparisons will be ordered (descending) in terms of their significance level and assessed using a p value <0.05 to determine statistical significance for the first comparison and p<0.025 for the second.

The main analysis for primary and secondary endpoints will use the full analysis set, consisting of all randomised patients, with participants analysed according to the group to which they were originally allocated, and with outcomes included irrespective of protocol adherence, in order to follow the *intention-to-treat* principle. The safety population, consisting of all patients who actually receive a trial intervention, according to the treatment received, will be used for analysis of toxicity and adverse events.

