#### Analysis

For analysis of the primary endpoint, the mean difference from baseline and week 32 will be presented with a corresponding 95% CI. Between-group differences will be analysed using linear regression techniques, analysing the week 32 values while including baseline covariate value. The effect of dapagliflozin will be estimated by contrasting (1) control arm versus dapagliflozin arm. The effect of exenatide will be estimated by comparing (2) dapagliflozin versus dapaglifozin and exenatide.

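### The 80% power is calculated for one unadjusted one-sided 5% test, but the analysis applies Hochberg thresholds to p-values of unstated sidedness and reports a 95% CI

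*Protocol article*

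**What the plan says.** All references are to the protocol article.

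- **Sample size.** Two comparisons are sized: arm B (dapagliflozin) vs A (placebo), and B vs C (dapagliflozin plus exenatide). "For both comparisons, a 1.5 kg in the change in body fat mass is considered a clinically relevant difference". The calculation is made "assuming 80% power and one-sided 5% significance level". On the original inputs, "36 patients per treatment arm were estimated to be required in order to adequately power the planned analysis". The revision after COVID-19 keeps the difference, significance level and power, changes the SD to 2.42 kg (effect size 0.62), and arrives at 33 per arm and 110 in total. No multiplicity adjustment is mentioned.
- **Significance levels.** Two primary comparisons are tested by Hochberg's procedure, with p<0.05 "to determine statistical significance for the first comparison and p<0.025 for the second". Sidedness is not given. The comparisons named here are C vs A and B vs A.
- **Analysis.** The mean difference between baseline and week 32 "will be presented with a corresponding 95% CI". The contrasts named are A vs B and B vs C.
- **Strengths and limitations list.** "The relatively small sample size provides sufficient power to answer the primary research question".

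**The concern.** The power figure describes a test that the analysis sections do not clearly use. A one-sided 5% test corresponds to a 90% CI, not a 95% CI. A single unadjusted test also ignores the 0.025 step, which applies whenever the other comparison fails at 0.05.

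The comparison of B with C carries the central hypothesis, that exenatide offsets the compensatory responses to dapagliflozin. On the two-sided reading, with Hochberg applied to the sized pair, a true 1.5 kg difference would be missed about 32% to 40% of the time rather than 20%. A null result read against a published statement of 80% power could be over-interpreted as no added benefit. Leaving sidedness open until after unblinding would also invite doubt about how it was chosen.

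**Working it through.** **Inputs (Sample size section).** Difference 1.5 kg; SD 2.55 kg originally (1.8 × √2 = 2.546) and 2.42 kg revised; 80% power; one-sided 5%; 33 evaluable per arm after the revision.

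**1. Reproducing the plan's figures.** n per arm = 2 × [(z for alpha + z for power) × SD / difference]².

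- One-sided 5%, SD 2.55: 2 × [(1.645 + 0.842) × 2.55/1.5]² = 35.7, so 36.
- One-sided 5%, SD 2.42: 2 × [(1.645 + 0.842) × 2.42/1.5]² = 32.2, so 33.
- Two-sided 5% (1.960 in place of 1.645): 45.4 and 40.9, so 46 and 41.

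The stated 36 and 33 therefore come from the one-sided, unadjusted test. On its own terms the arithmetic is right.

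**2. Power of a single test at 33 per arm.** Standard error = 2.42 × √(2/33) = 0.596 kg; noncentrality = 1.5/0.596 = 2.518; 64 degrees of freedom; noncentral t distribution.

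| Test | Critical t | Power | n per arm for 80% |
|---|---|---|---|
| One-sided 5% | 1.669 | 80.1% | 33 |
| Two-sided 5% | 1.998 | 69.8% | 42 |
| Two-sided 2.5% | 2.295 | 59.0% | 51 |

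**3. Power under Hochberg on the two sized comparisons.** Both are declared significant if the larger p is below 0.05; otherwise only a comparison with p below 0.025 is. Simulation used three arms of 33, arm B shared, pooled variance and 400,000 runs.

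| Sidedness of p | Both effects 1.5 kg: each | Both effects 1.5 kg: both shown | Only one real: that one |
|---|---|---|---|
| Two-sided | 68% | 44% | 60% |
| One-sided | 79.5% | 62% | 71% |

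Most of the loss comes from sidedness. Hochberg costs about 2 points if both effects are real and about 10 if only one is.

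**4. Test and interval, if p is one-sided.** At SD 2.42 kg, a difference reaches one-sided p<0.05 at 1.669 × 0.596 = 0.99 kg, while a 95% CI excludes zero only from 1.998 × 0.596 = 1.19 kg. A difference between these values could be declared significant, provided the other comparison also has p<0.05, while its 95% CI includes zero. One-sided p<0.025 has the same boundary as the 95% CI, so no conflict arises at that step.

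**5. Baseline adjustment.** The SD used is described as that of the change from baseline. With equal variances at the two visits, adjusting for baseline multiplies the change-score variance by (1 + ρ)/2, where ρ is the baseline/week-32 correlation. The protocol gives no ρ, so these values are assumptions.

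| Assumed ρ | Variance factor | Effective SD (kg) | Power, two-sided 5%, single test |
|---|---|---|---|
| 0.95 | 0.975 | 2.39 | 71% |
| 0.8 | 0.90 | 2.30 | 74% |
| 0.5 | 0.75 | 2.10 | 82% |

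**6. The Hochberg family as literally written (B vs A, C vs A).** Assuming additive effects of 1.5 kg and 3 kg, power for B vs A is about 70% two-sided and 80% one-sided. C vs A almost always succeeds, so Hochberg costs essentially nothing. B vs C then lies outside the procedure.

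**The case against.** A reader might infer that the trial simply does not deliver its 80% and misses a 1.5 kg effect 30% to 40% of the time under its own analysis rule. The text does not support that unconditional statement, for four reasons.

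- **Sidedness is open.** The only sidedness stated anywhere is one-sided. If the Hochberg p-values are one-sided and both effects are 1.5 kg, the difference the plan calls relevant for both comparisons, power is 79.5% each and the stated figure essentially stands. It still falls to 71% if only one effect is real.
- **The CI is weak evidence.** The 95% CI is attached to the difference between baseline and week 32, which may mean change within an arm. In any case, reporting a 95% CI does not fix the sidedness of a test. The separate analysis plan may settle it.
- **The Hochberg figures need a choice.** The 68%, 44% and 60% apply to B vs A and B vs C. The Significance levels section names C vs A and B vs A, so these are not powers under that section as written.
- **Baseline adjustment cannot be dismissed on one assumed correlation.** At 0.5 it would restore the two-sided 5% single-test figure to about 82%. High correlation is plausible for fat mass, but the protocol does not give it.

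All four stand as limits on the size of the problem. They do not remove it: the protocol itself fixes a sizing alpha, decision thresholds and a power claim, and does not make them agree. Nor is this an arithmetic error, since the calculation is correct for the test it names and the one-sided level is openly disclosed.

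**Conclusion.** The point holds as a mismatch between sizing alpha and decision rule, and its size depends on what the p-values turn out to be.

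- **Two-sided, as is conventional with a 95% CI:** about 70% for a single test at 5%. With Hochberg on the sized pair, 60% to 68% per comparison, and 44% for both when both effects are real.
- **One-sided:** close to the stated 80% per comparison only if both effects are 1.5 kg; 71% if only one is real. Significance and a between-group 95% CI can then disagree.

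These figures assume 33 evaluable patients per arm, a 1.5 kg difference, SD 2.42 kg and no gain from baseline adjustment; that gain is small if the baseline/week-32 correlation is high.

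**What to change.** 1. State the sidedness of the primary tests once and use it in the Sample size, Significance levels and Analysis sections. Two-sided matches the 95% CI; one-sided testing would need matching intervals.
2. Reconcile the Hochberg family in Significance levels (C vs A, B vs A) with the comparisons in Sample size and Analysis (B vs A, B vs C). The Sample size section says that C vs A will not be reported.
3. Restate the power delivered at 33 per arm under the resulting rule, separately for both effects real and only one real. If credit is taken for baseline adjustment, give the assumed correlation.
4. Qualify the statement on power in the strengths and limitations list accordingly.

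The protocol describes recruitment as ongoing, so this can be settled before unblinding. It asks for no extra patients, visits or procedures; the only cost is a less favourable stated power.
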